## Abstract

**Background:**

The burden of chronic pain is a major challenge, impacting the quality of life of patients. Intensive programmes of mindfulness-based therapy can help patients to cope with chronic pain but can be time consuming and require a trained specialist to implement. The self-management model of care is now integral to the care of patients with chronic pain; home-based interventions can be very acceptable, making a compelling argument for investigating brief, self-management interventions. The aim of this study is two-fold: to assess the immediate effects of a brief self-help mindfulness intervention for coping with chronic pain and to assess the feasibility of conducting a definitive randomized controlled trial to determine the effectiveness of such an intervention.

**Methods/Design:**

A randomized controlled pilot study will be conducted to evaluate a brief mindfulness intervention for those with chronic pain. Ninety chronic pain patients who attend hospital outpatient clinics will be recruited and allocated randomly to either the control or treatment group on a 1:1 basis using the computer-generated list of random numbers. The treatment group receives mindfulness audios and the control group receives audios of readings from a non-fiction book, all of which are 15 minutes in length. Immediate effects of the intervention are assessed with brief psychological measures immediately before and after audio use. Mindfulness, mood, health-related quality of life, pain catastrophizing and experience of the intervention are assessed with standardized measures, brief ratings and brief telephone follow-ups, at baseline and after one week and one month. Feasibility is assessed by estimation of effect sizes for outcomes, patient adherence and experience, and appraisal of resource allocation in provision of the intervention.

**Trial registration:**

ISRCTN61538090 Registered 20 April 2015

**Electronic supplementary material:**

The online version of this article (doi:10.1186/s13063-016-1405-2) contains supplementary material, which is available to authorized users.

## Background

The burden of chronic pain is a major challenge within healthcare, as approximately 14 million people in England alone currently live with chronic pain [1]. Chronic pain has a negative impact on quality of life [2] and results in high levels of disability [3], with 41 % of patients attending pain clinics reporting being unable to work [4]. Furthermore, high comorbidity rates of depression and anxiety [5] are common, with the 2008 Chief Medical Report stating that 16 % of sufferers report that their chronic pain is so bad that they sometimes want to die [6]. In the UK, the cost for back pain alone has been estimated at £12 billion per annum, which may be partially explained by the fact that, as is reported [6], 25 % of pain sufferers lose their jobs.

Psychological therapies, most commonly in the form of cognitive behavioural therapies [7, 8], have been shown to play an important role in helping patients cope with chronic pain [9, 10]. More recently, mindfulness-based approaches have emerged [11], involving training patients to engage in self-regulation of attention through increasing awareness of, and accepting, present thoughts, feelings and physical sensations [12].

Among those with chronic pain, mindfulness interventions have been shown to reduce anxiety, depression and distress, and to enhance quality of life [13]. Recent UK National Health Service (NHS) guidelines include a recommendation for mindfulness meditation in treating depression [14]. There is also evidence that regular mindfulness meditation modulates neural mechanisms [15, 16], especially those related to pain, as well as benefits for inflammatory systems [17].

While this research is promising, a major barrier with the implementation of current mindfulness interventions is the amount of time they require and the necessity of a trained specialist to oversee them [18]. Mindfulness programmes typically involve weekly group-based sessions over 8 weeks and many chronic pain patients do not have the resources, physically or mentally, to engage with such an intensive programme [19, 20]. Self-help type interventions, which offer more autonomy, are likely to be more adaptable for many such patients and the self-management model of care is now an integral part of the NHS [21]. This model has led to the development of a breadth of interventions with some evidence for efficacy ranging from web-based interventions to brief interventions that patients can readily use as part of a self-care programme.

One type of brief intervention that fits this profile is a short mindfulness-based body or breathing scan. These scans are a key component of mindfulness meditation practice; they involve being directed to focus attention on the present moment through observing the breath and bodily sensations, while becoming aware of, and accepting without judgement, any thoughts and feelings which arise. The traditional mindfulness-based stress reduction intervention includes a body scan [22], lasting anything from 5 to 45 minutes.

There has been little research testing brief mindfulness interventions in either clinical or non-clinical populations. Investigations with healthy populations with a brief mindfulness intervention have been successful in demonstrating a reduction in some aspects of the pain experience, such as distress and sensitivity, during experimental pain studies [23, 24]. An audio-guided 10 minute mindfulness body scan has also been shown to reduce tobacco cravings among abstinent smokers [25, 26]. In a chronic pain population, encouraging effects were found, with an audio recording of a 10-minute body scan reducing reports of distress immediately after listening to the audio in a clinical setting [27]. The intervention evaluated in the current study is a refinement of the intervention used in the latter.

### Aims and objectives

The aim of this paper is to describe the protocol for a pilot randomized controlled trial designed with two primary objectives: assessment of the immediate effects of a brief mindfulness-based intervention on patients with chronic pain and evaluation of the intervention to assess the feasibility of conducting a definitive randomized controlled trial. As regards to the immediate effects of the intervention, it is hypothesized that the intervention will result in a significant reduction in ratings of pain-related symptoms and distress.

## Methods/Design

### Study design

This is a single centre, parallel group, randomized controlled pilot study (see Fig. 1 for a flowchart), designed to assess the immediate effects of a mindfulness-based intervention, as well as the feasibility of conducting a definitive randomized controlled trial.

**Fig. 1 Fig1:**
[figure not shown]
Flow diagram of the feasibility study design assessing the effects of a brief mindfulness intervention for those living with chronic pain

### Participants and setting

Patients are being recruited from three outpatient NHS physiotherapy/pain clinics at St. George's University Hospitals NHS Foundation Trust. All patients are initially screened by the appropriate clinician (i.e. physiotherapist or pain consultant). Those who meet the inclusion criteria are given a patient information sheet by the clinician and are asked whether they consent to have their contact details passed to a researcher who will call them to discuss whether they wish to join the study or if they would like to meet with the researcher in person to discuss the study.

Patients are eligible if they meet the following criteria: (1) over 18 years of age; (2) living with chronic pain (i.e. those who live with a diagnosis of chronic pain or those who have had pain for more than three months after the time healing should have occurred [19]); and (3) able to hear audio recordings or have their own equipment to enable them to do so.

Patients are excluded if they are (1) considered by the clinician to be too unwell to participate or (2) unable to speak or read English sufficiently to understand and complete the self-administered questionnaires.

### Sample size

It is recommended that pilot/feasibility studies ideally recruit a total of at least 50 participants [20], although in practice many studies recruit 50–100 participants. We aim to recruit 90 participants (45 in each treatment arm). Then, allowing for 10 participants withdrawing (estimate based on a previous mindfulness study with the same population [27]), we aim to have around 80 participants with data through to the final one month follow-up. Moreover, based on a finding from a previous similar study [27], we used a Wilcoxon signed-rank test (G-Power software) to calculate that a total sample size of at least 50 participants would be required to detect a significant difference of 1.2 (SD = 2) on the perceived distress scale, between the two groups (immediately) after the intervention. This was with 80 % power at the 5 % significance level.

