### Statistical analysis

We will present the baseline characteristics according to the two study groups. For the analysis assessing the immediate effects of the intervention, we will assess the effect of the body scan versus the control intervention on ratings for the brief psychological measures administered immediately before and after the interventions. This analysis will be conducted for the ‘before’ and ‘after’ ratings in the clinic and also for those conducted in the participant’s own environment. First, we will compute change scores by subtracting post-intervention scores from pre-intervention scores. As it is a pilot study with a small sample size, initially we will assess the effect of the treatment groups on outcomes (i.e. change scores) using *t* tests or Mann–Whitney tests. We will then conduct multiple linear regressions with the change scores as the dependent variables and treatment groups as the independent variable. Statistical significance will be assessed with the likelihood-ratio test, with the estimate of effect given as mean difference of change scores and 95 % confidence interval. As a secondary analysis we will adjust for age, sex and baseline BPI score, as potentially important prognostic baseline factors. We will also inspect the baseline characteristics, for the two groups, to assess whether there are any other potential confounders that need to be controlled for.

Next, we will assess the effect of the study groups on outcomes recorded at baseline and one month. All participants with data at both time points will be included in the analysis. It is unlikely that the study will be sufficiently powered to detect significant differences between the groups but we will carry out analyses in order to inform parameters for a definitive trial. We will compute change scores between baseline and one month for the HADS, EQ-5D-5 L, PCS and the CAMS-R, and we will conduct multiple regressions, with adjustments as above. We will also repeat this procedure for the CAMS-R at baseline and one week.

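### The sample-size sentence uses a paired signed-rank calculation for a comparison of two independent groups; on its stated inputs, 50 in total gives about 53–55% two-sided power, not 80%

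*Protocol article*

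**What the plan says.** All references are to the protocol article.

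- **Design.** Study design states: "This is a single centre, parallel group, randomized controlled pilot study". Allocation is 1:1.
- **Recruitment.** Sample size sets a target of 90 participants, 45 per arm. It supports this first by guidance on the size of pilot studies and then by "allowing for 10 participants withdrawing", which leaves around 80 with data at one month.
- **Power statement.** The same section then adds: "we used a Wilcoxon signed-rank test (G-Power software) to calculate that a total sample size of at least 50 participants would be required". The target is "to detect a significant difference of 1.2 (SD = 2) on the perceived distress scale", and the contrast is "between the two groups (immediately) after the intervention". It closes: "This was with 80 % power at the 5 % significance level". It does not say whether the test is one- or two-sided.
- **Planned analysis.** Statistical analysis states: "First, we will compute change scores by subtracting post-intervention scores from pre-intervention scores". The change scores are then compared between arms by t or Mann–Whitney tests, followed by linear regression on treatment group. This is done for the clinic session and again for the session at home.

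**The concern.** The test used for sizing matches neither the design, nor the contrast in its own sentence, nor the planned analysis. A signed-rank calculation has one set of differences and one source of sampling error. A comparison of two arms has two. For the same standardised effect the two-arm comparison needs roughly twice as many participants in each arm as the paired test needs pairs, so a total of 50 built on the paired figure is too small by nearly a factor of two.

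There is a second ambiguity. The sentence describes a difference after the intervention, while the analysed variable is the change score. The reader cannot tell which of these has the SD of 2.

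The immediate effect is one of the two primary objectives, and the protocol hypothesises a significant reduction. The remark under Statistical analysis that power is unlikely to be sufficient concerns the one-month outcomes, not this one. Someone who reads a non-significant immediate result against the statement that 50 gives 80% power would give it more weight than it deserves.

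**Working it through.** **Inputs.** From Sample size: difference 1.2, SD 2, power 80%, significance level 5%, stated total 50, planned 45 per arm, about 80 remaining at one month. From Statistical analysis: t or Mann–Whitney test between arms. Assumed: two-sided testing (one-sided also shown), and SD 2 as the between-participant SD of the analysed variable (relaxed in step 5).

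Standardised effect: d = 1.2 / 2 = 0.6.

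**1. Reproducing the 50.** Power comes from the noncentral t distribution. For a rank test, n is multiplied by the asymptotic relative efficiency 3/π = 0.955 (normal data). For the signed-rank test the noncentrality is d·√(0.955·n), with 0.955·n − 1 degrees of freedom.

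- n = 24: power 78.4%.
- n = 25: noncentrality 0.6·√23.87 = 2.93; power 80.1% (simulation 80.2%).

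The minimum is 25 observations, and 2 × 25 = 50 equals the stated total. The protocol does not describe this doubling; it is the explanation that fits.

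**2. The same 50 as a two-arm comparison.** The noncentrality is d·√(n/2) with n per arm and 2n − 2 degrees of freedom; for Mann–Whitney, n is replaced by 0.955·n.

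- t test, 25 per arm: 0.6·√12.5 = 2.12 on 48 degrees of freedom; power 54.7%.
- Mann–Whitney, 25 per arm: noncentrality 2.07; power 52.8% (simulation 52.2%).
- One-sided 5%: 67.2% (t) and 65.4% (Mann–Whitney).

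**3. Size needed for 80% power.**

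| Test | Two-sided | One-sided |
|---|---|---|
| t | 45 per arm (90 in total) | 36 per arm (72) |
| Mann–Whitney | 47 per arm (94 in total) | 37 per arm (74) |

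If the named test were only a slip for Mann–Whitney, 50 would still not follow from the stated inputs.

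**4. What the planned numbers give, two-sided.**

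| Analysed | t | Mann–Whitney |
|---|---|---|
| 90 (45 per arm) | 80.4% | 78.5% |
| 80 (40 per arm) | 75.5% | 73.5% |

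**5. Sensitivity to the meaning of SD 2.** Randomisation makes the expected baselines equal, so a difference of 1.2 in the post-audio rating is also the expected difference in change. The SD does not carry over in the same way. If 2 is the SD of the rating itself, equal before and after, the change-score SD is 2·√(2(1 − r)), where r is the pre–post correlation. The protocol does not give r, so the values below are assumptions.

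| r | Change-score SD | Two-sided t-test power, 25 per arm |
|---|---|---|
| 0.3 | 2.37 | 42.0% |
| 0.5 | 2.00 | 54.7% |
| 0.7 | 1.55 | 76.5% |
| 0.75 | 1.41 | 83.6% |

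The 53–55% figure therefore holds when SD 2 is the SD of the analysed variable, or equivalently when r = 0.5.

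**The case against.** The best defence is that this is a supplementary sentence in a pilot. The 90 is justified by pilot convention and expected withdrawals, and the power calculation is added afterwards. That stands. A reader might infer that the plan offers the excess of 90 over 50 as a safety margin for power, but the text never says so.

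A second objection is that the clinic ratings are taken during the first visit, before one-month attrition can occur. That also stands. A reader might infer that the expected 80 completers leave the main immediate comparison short of power, but that 80 is the number with data at one month. For the clinic ratings the relevant number is close to 90. Only the home-session ratings, returned by diary, could plausibly fall to 80.

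Third, the shortfall depends on what SD 2 describes. It comes from a previous study that is not shown, and step 5 shows that a strong pre–post correlation could bring 50 up to 80% power for the change score. This makes the size of the error conditional. It does not rescue the sentence, which names the wrong test and gives no correlation. If SD 2 were the SD of paired differences, the calculation would answer a within-group question and not the between-group one stated.

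Fourth, the hypothesis is directional and sidedness is not stated. One-sided testing raises power with 50 to 65–67%, still below 80%.

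Finally, results will be reported as mean differences with 95% confidence intervals, which would show the imprecision of a null finding. This limits the harm from misreading but leaves the stated figure wrong.

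**Conclusion.** The error is real. A paired or one-sample calculation supports a claim about two independent groups, and the total of 50 does not follow from the stated 1.2, SD 2, 80% and 5% under a standard two-sample test. This assumes that SD 2 belongs to the analysed variable and that the data are roughly normal. Under those assumptions power with 50 is about 53–55% two-sided, and 80% needs 90 (t test) or 94 (Mann–Whitney) in total.

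The documents do not support the stronger conclusion that the trial is too small or must recruit more. The planned 90 gives close to 80% for the clinic ratings under the same assumption. Nor do they show that SD 2 is the change-score SD; that is for the authors to state. The point should be corrected, but it changes a stated figure and not the design, the enrolment or the analysis.

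**What to change.** 1. Replace the power sentence with an independent-groups calculation that matches the t or Mann–Whitney comparison under Statistical analysis, and remove the minimum of 50 as a power statement.
2. State whether the 5% level is one- or two-sided.
3. State whether SD 2 is the SD of the post-audio rating or of the change score. If it is not the SD of the variable analysed, insert the right one and recompute.
4. If SD 2 does apply to the analysed variable, the text could read: a difference of 1.2 (SD 2) between two independent groups needs 45 per arm (t test) or 47 per arm (Mann–Whitney) for 80% power at two-sided 5%; with 90 analysed, power for the clinic ratings is about 80% or 78.5%; if only 80 home-session ratings are returned, power for those is about 75% or 73%.

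The cost is one rewritten sentence and a check of the source of the SD. No extra participants are needed and the analysis is unchanged.

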### Randomization

An independent statistician generates a randomization list using the online resource ‘Research Randomizer’. This list is used by researchers to allocate volunteers to either the control or treatment group on a 1:1 basis. Patients are allocated their number in ascending order based on their order of enrolment. Allocation is concealed from the participant and researcher until all baseline assessments have been completed. Due to limited resources, the same researcher delivers the intervention and administers the research measures, and therefore treatment allocation cannot be concealed from the researcher. Thus, neither participants nor researchers are blinded to treatment allocation during intervention delivery or during outcome assessment. An independent statistician, who is blinded to the treatment allocation, will complete the initial analysis for the main outcomes.

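### The stated 80% power with a total of 50 does not describe the planned analysis, a two-group comparison of change in distress

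*Protocol article*

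**What the plan says.** The protocol article, under Sample size, first justifies its recruitment target on pilot-study grounds: "We aim to recruit 90 participants (45 in each treatment arm"). The target includes a margin for loss to follow-up, "allowing for 10 participants withdrawing". A power calculation based on an earlier, similar study comes next. Its method is given as "we used a Wilcoxon signed-rank test (G-Power software) to calculate". Its result is that "a total sample size of at least 50 participants would be required", and the effect it targets is a "difference of 1.2 (SD = 2) on the perceived distress scale, between the two groups (immediately) after the intervention". The section closes: "This was with 80 % power at the 5 % significance level". It does not state whether the test is one- or two-sided.

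Under Statistical analysis, the immediate effect is handled differently: "First, we will compute change scores by subtracting post-intervention scores from pre-intervention scores". Those change scores are compared between the arms by t or Mann-Whitney tests and then serve as the dependent variable in linear regression. The reported estimate is the between-arm mean difference in change with its 95% confidence interval. No analysis of the immediate ratings takes the post-audio score as the outcome. The adjusted model adds age, sex and baseline BPI, not the pre-audio distress rating.

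**The concern.** The immediate effect is one of the two primary objectives (Aims and objectives), and it carries a hypothesis of a significant reduction in symptom and distress ratings. A power statement attached to it should describe the test that will be run. This one differs from the analysis in two respects.

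- **Variable.** The sizing refers to distress after the intervention, the analysis to change from before to after. Under randomization the expected group difference is the same for both, but the SD is not.
- **Test.** A signed-rank test is a paired or one-sample procedure. The analysis compares two independent arms.

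If the figure of 50 is taken at face value, the 90 planned patients look like a generous margin over what is needed. A null result on change would then be read against a power figure that does not belong to it. The stated SD could also be carried into the sizing of the definitive trial that this pilot is meant to inform.

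**Working it through.** **Inputs.** From Sample size: difference 1.2, SD 2, hence standardized difference 1.2/2 = 0.6; power 80%; level 5%; stated total 50; planned total 90, 45 per arm. From Randomization: 1:1 allocation. From Statistical analysis: two-group comparison of change. Assumed: two-sided testing and, where needed, a pre-post correlation r.

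**Step 1: reproduce the figure of 50.**

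As a two-group comparison, n per arm = 2(1.960 + 0.842)² / 0.6² = 2 × 7.85 / 0.36 = 43.6, so 44 per arm and 88 in total. The noncentral-t calculation gives 45 per arm (90). The Mann-Whitney test with normal data (relative efficiency 3/π) gives 47 per arm (94). One-sided, the totals are 70, 72 and 74. None of these is 50.

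As a signed-rank test with standardized difference 0.6, 25 pairs give 80.1% power (79.8% by simulation). Twice 25 is 50. This is the likely origin of the figure, but it is inferred from the match; the document does not say so.

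**Step 2: power of a two-group test at the stated total of 50, if SD 2 applies to the analysed variable.**

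With 25 per arm the noncentrality is 0.6 × √(25/2) = 2.12. Power is 55% by t test and 53% by Mann-Whitney (51% by simulation), not 80%. With 45 per arm the noncentrality is 0.6 × √(45/2) = 2.85, and power is 80% (t) or 79% (Mann-Whitney).

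**Step 3: if SD 2 is the SD of the raw score, the same before and after.**

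The SD of change is 2 × √(2(1 − r)). The expected group difference stays at 1.2. Two-sided t test:

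| r (assumed) | SD of change | Power, total 50 | Power, total 90 | Total for 80% |
|---|---|---|---|---|
| 0.3 | 2.37 | 42% | 66% | 126 |
| 0.5 | 2.00 | 55% | 80% | 90 |
| 0.6 | 1.79 | 64% | 88% | 72 |
| 0.7 | 1.55 | 77% | 95% | 56 |
| 0.8 | 1.26 | 91% | 99% | 38 |

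A total of 50 reaches 80% only when r is about 0.72 (SD of change about 1.48). At r = 0.5 the raw and change SDs coincide, so that row also applies if SD 2 is already the SD of change.

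**Step 4: can the document settle which SD is meant?**

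No. The wording about a difference after the intervention suggests a raw post score. The signed-rank test, whose effect size is a mean difference divided by the SD of differences, suggests a change. The rating scale does not decide it. Baseline data collection gives the brief items as 1 to 5, while the later section describing those items gives 1 to 7. The largest possible SD of a raw score is about (5 − 1)/2 = 2 on the first scale and (7 − 1)/2 = 3 on the second. A raw SD of 2 would thus be extreme on one scale and plausible on the other.

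**The case against.** Several points on the other side carry weight.

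- **The stronger reading is not established.** A reader might infer that the trial was sized on the post-audio score, that this endpoint is never tested, and that the trial is therefore underpowered. The document does not support this. It does not say that SD 2 belongs to the post score. The treatment contrast is the same for post and change scores under randomization. Using change lowers power only if r is below 0.5 and raises it above 0.5. The same single items are rated before and after one 15-minute audio at one visit, so a low r is arguably the less natural assumption, though that too is an assumption.
- **The recruitment target does not rest on this calculation.** Ninety is justified first by pilot-study practice, and the power statement is an addition to it. Results will be reported with confidence intervals, so a null finding would not be judged on the power figure alone.
- **A missing correlation is a detail an article may leave out.** This is accepted, and the absence of r is not the point made here.

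What remains is not an omission. The article states a test, a variable and a total, and its own analysis section uses a different test and a different variable. If SD 2 is the SD of change, the total of 50 is wrong for the planned comparison. If SD 2 is the raw SD, 50 is enough only when r is about 0.72 or higher, a condition that nothing in the text supplies.

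**Conclusion.** The point holds as a mismatch between the stated power and the planned analysis. With difference 1.2, SD 2 taken as the SD of change, and a two-sided 5% test, a total of 50 gives about 55% power, and 80% needs about 90 (t) or 94 (Mann-Whitney). With SD 2 taken as the raw SD, power at 50 runs from 42% (r = 0.3) to 77% (r = 0.7), and at the planned 90 from 66% to 95% over the same range.

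It does not follow that the trial is too small. Power at 90 may lie on either side of 80%, and the document cannot settle which. The 90-patient figures also assume that every patient gives both clinic ratings. That is reasonable because both are taken at one visit, whereas the withdrawal allowance concerns follow-up to one month. The practical consequence is moderate: the planned number may well be adequate, but the stated minimum of 50 and its 80% should not stand.

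**What to change.** In the Sample size section:

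1. Restate the calculation as a two-sample comparison (t or Mann-Whitney) of mean pre-to-post change in distress, with a between-arm difference of 1.2, and say whether it is one- or two-sided.
2. State which SD the 2 is. If it is the SD of change, describe the difference as one in change. If it is the raw SD, give the SD of change from the earlier study's paired ratings, or the assumed r.
3. Replace the total of 50 with the figure this gives: about 90 (t) or 94 (Mann-Whitney) if the SD of change is 2.
4. Report the power for 90 patients, over r = 0.3 to 0.7 if r is not known.
5. Reconcile the 1-to-5 and 1-to-7 descriptions of the brief ratings, so that the scale behind 1.2 and 2 is clear.

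The cost is one recalculation and a few sentences. Restating the calculation does not itself call for more patients, since 90 also stands on pilot grounds. The drawback is that the stated minimum rises and the apparent margin over it shrinks or disappears if the SD of change is about 2 or more.
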